### 3.6 Explanation for choice of comparator (or placebo)

Not applicable.

### 3.7 Risks / Benefits

#### 3.7.1 Risk analysis

A risk assessment has been performed according to EN ISO 14971 (see Appendix Risk Management 17.6.). The results are presented below.

The risk assessment shows that no unacceptable residual risks are identified. Mitigating controls and procedures have been identified to any risk higher than acceptable risks.

Concerning Data Safety, Data Flow and Analysis an internal (University Hospital Basel (USB)) consortium was established and alignment with data security officers (university and hospital) as well as the legal head of the hospital was achieved.

#### Summary

The risk analysis concludes that no unacceptable residual risks are identified and no serious adverse effects are expected from the use of the device or participation in the study.

The study is not expected to directly benefit the study participants. But the results will enable the sponsor to perform the following validation study and therefore contribute to the development of reliable and valid digital biomarkers as a promising tool to improve patient monitoring and management.

#### 3.7.2 Post-trial care

No post-trial care is needed, as this is not an interventional study.

#### 3.7.3 Competing studies

No validated and comprehensive suite of digital markers exists up to now. As mentioned in section 3.1 the DREAMS App is unique by its comprehensive set of active challenges, gamified neuropsychological assessment, passive monitoring and questionnaires. The systematic approach with a clinical feasibility study and the following validation study will ensure, that the selection of biomarkers will enable better monitoring and eventually better and personalized treatment of PwMS.

### **3.8 Justification of choice of study population**

Patients under the care of our Multiple Sclerosis Center who are representative for the general MS population will be approached and included (age range 18-70, EDSS 0-6.5) In addition a group of age- and sex- matched healthy controls will be included.

Patients and Healthy controls will need to possess a Smartphone and be able to use the App (sufficient vision, no major cognitive deficits, no major motor and dexterity impairment that would preclude safe administration of the App challenges).

## **4. STUDY OBJECTIVES**

### **4.1 Overall Objective**

The objective of this feasibility study is to identify digital biomarkers that are technically reliable and measurable as well as meaningful to patients with MS.

### **4.2 Primary Objective**

The primary objective of this study is to identify digital biomarkers that are technically reliable and measurable, and perceived as user friendly and meaningful for patients with MS (PwMS).

### **4.3 Exploratory Objectives**

The exploratory objective of this study is to find differences on these biomarkers between 30 PwMS and 30 age- and sex- matched healthy controls (HC) on a group level.

### **4.4 Safety Objectives**

Not applicable.

## **5. STUDY OUTCOMES**

### **5.1 Primary Outcome**

The primary study outcomes are:

1. Test reliability of digital biomarkers measured by Intra Class Correlation ( $ICC \geq 0.6$ )
2. Test reliability of digital biomarkers measured by Coefficient of variation ( $CV < 20\%$ )
3. Determination of user acceptance of digital biomarkers with regards to acceptance based on questionnaire ( $>3$  on a Likert Scale)

### **5.2 Exploratory Outcomes**

Exploratory study outcome is to identify digital biomarkers that:

- a.) differentiate on a group level between PwMS and age- and sex- matched healthy controls (HC).
- b.) correlate with already established assessment tools in their respective domains (e.g. "Catch-a-cloud" vs. Nine-Hole-Peg test).

### **5.3 Other Outcomes of Interest**

-

### **5.4 Safety Outcomes**

Not applicable.

## **6. STUDY DESIGN**

### **6.1 General study design and justification of design**

This feasibility study is a prospective observational proof of concept study in patients with MS with a control group of healthy volunteers. Duration of the study will be 6 weeks per patient. This study is the first step to identify precise, well accepted and meaningful digital biomarkers for patients with multiple sclerosis as a first step towards validation in further studies. Digital biomarkers will be captured by patient's own smartphones (iOS and Android) and by an additional smartwatch (Fitbit Versa 2). The smartwatches will be given to all participants and will be handed over to them after the study end (market value CHF 210/smartwatch).

30 patients with MS and 30 age- and sex- matched healthy controls will be included. All participants will be instructed by a study nurse at the beginning of the study to assure that all patients and healthy controls will use the App and perform all tasks in a similar and correct way. Within the study all participants will perform all tests repeatedly over a time period of 5 weeks (every test twice a week resulting in 10 repetitive performances/test). In week number 6 they will perform all questionnaires and will have their semi-structured interview.

This feasibility study aims to select the most reliable and meaningful biomarkers out of over 20 candidate biomarkers developed by our team.

Ranking of test performance will be done for each of the digital biomarkers by:

- Intra Class Correlation of at least 0.6 if repeated 10 times within 6 weeks
- Coefficient of variation must be less than 20% if repeated 10 times within 6 weeks
- User acceptance as assessed by a feedback questionnaire and a semi-structured interview at the end of the study (>3 on a likert scale).

For detailed criteria of performance see Chapter 11. Statistical Methods, 11.4.2. Primary Analysis.

For the exploratory analysis (potential differences between healthy controls and PwMS on a group level and correlation with already established assessment tools in their respective domains) age- and sex matched healthy controls will be included who will follow an identical test schedule and also provide their feedback about the App.

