#### a. Mobile app

1. User authentication, schedule and reminders for the patients, available in German, English and Spanish
2. Domains and challenges included (challenges names are listed as they will appear in the german version, table 3):

Table 3

| Domain            | Challenges & Scales                                                                           |
|-------------------|-----------------------------------------------------------------------------------------------|
| Movements         | La Promenade
Pinguin
The Butler
Musical Chairs
Spanische Treppe
Schweizergarde |
| Fine motor skills | Catch-A-Cloud
Konfetti
Flame dodge (Left)
Flame dodge (Right)                        |
| Vision            | Adlerauge
Nebel                                                                            |

|                                      |                                                                                                                                                 |
|--------------------------------------|-------------------------------------------------------------------------------------------------------------------------------------------------|
| Cognition                            | SDMT
Word Hunt
Spin Cycle
Low Pop
Puzzle Blox
Perilous Path
Baggage Claim
Must Sort
Rush Back
Face Switch
Zap Gap |
| Validated scales and Symptom Tracker | MSIS-29
MSWS-12
Fatigue Severity Scale
MS symptom Tracker
Feedback questionnaire                                                    |
| Relapse report                       | Relapse reporting                                                                                                                               |
| Passive monitoring                   | FitBit                                                                                                                                          |

*Table 3: Domains and challenges included*

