### 3.5 Medical Device: Rationale for the intended purpose in study (pre-market MD)

#### 3.5.1 Introduction

The study team aims to capture 10 data repeats per task and study participant for all tasks within the 6 weeks study period. A weekly schedule has been developed and supports that goal (see table 5). The schedule is developed such that participants are requested to perform different challenges every day to prevent a high level of repetition.

- Challenges must be performed during 5 days every week, participant can select which 5 days work best for him/her
- Total time spent on performing scheduled exercises should be maximum 15-20 minutes per (active) day
- The schedule should minimize having multiple strenuous exercises ("La promenade", "Musical Chairs" and "Spanische Treppe") on one day. If the schedule is too demanding for one day, participants can defer challenges to another day.
- Study nurse will be alerted if user completes < 75% of exercises (i.e. missing >2) for at least 2 out of 5 days
- Users can choose the order of challenges for one day, challenges are categorized in activity challenges and cognitive games
- Only fully completed challenges are registered, marked as completed and sensor data is collected successfully. For not completed challenges information about the event is recorded for further improvement of the app development and sensor data is not collected.
- Users will not be able to perform challenges or play games outside the schedule
- Study nurse will train the participant to make sure that all tasks are fully understood and are performed correctly
- I can't do this:
  - User can indicate that he/she wants to postpone exercise to later in the week (one of the 2 free days)
  - Maximum of 4 exercises can be moved to each of these 2 days
- System of reminders is in place for participants to complete daily schedule

Table 5

| Challenge schedule: Weeks 1 - 6 |                                                      |            |           |       |       |       |       |                                     |
|---------------------------------|------------------------------------------------------|------------|-----------|-------|-------|-------|-------|-------------------------------------|
| #                               | Challenge Name                                       | Time (sec) | Weeks 1-5 |       |       |       |       | Week 6                              |

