| 26                              | Fatigue Severity Scale                               | 120        |           |       |       |       |       | Day 2                               |
| 27                              | MS Symptom Tracker                                   | 120        |           |       |       |       |       | Day 3                               |
| 28                              | Feedback Questionnaire and Semi-Structured Interview | 1'800      |           |       |       |       |       | Day 4 or 5                          |
|                                 | Total time per day (min)                             |            | 10.2      | 10.7  | 10.3  | 9.7   | 11.0  | Day 1: 10
Day 2: 10
Day 3: 10 |

|  |                         |  |   |   |    |   |    |                   |
|--|-------------------------|--|---|---|----|---|----|-------------------|
|  |                         |  |   |   |    |   |    | Day 4 or 5:
40 |
|  | Number of
challenges |  | 7 | 7 | 11 | 7 | 11 |                   |

Table 5: Weekly Schedule

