### **11. STATISTICAL METHODS**

#### **11.1 Hypothesis**

Null Hypothesis: It is not possible to identify reliable, well accepted biomarkers.

Alternative Hypothesis: It is possible to identify at least one reliable, well accepted biomarker for the following domains: a) vision b) cognition c) dexterity d) movement.

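### The text promises 10 repetitions of every test, but Table 5 schedules both vision tests and mSDMT once a week, so the whole vision domain rests on 5

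*Protocol*

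**What the plan says.** The synopsis (Study design) and section 6.1 describe 5 weeks of testing with "every test twice a week resulting in 10 repetitive performances/test". Section 3.5.1 sets the same target, "The study team aims to capture 10 data repeats per task and study participant for all tasks within the 6 weeks study period", and presents the weekly schedule in Table 5 as supporting it.

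Section 6.1 then writes the number into both reliability criteria: "Intra Class Correlation of at least 0.6 if repeated 10 times within 6 weeks" and "Coefficient of variation must be less than 20% if repeated 10 times within 6 weeks". For detail it refers to section 11.4.2, where the thresholds are an ICC of at least 0.6 and a median CV below 20%, with no repeat count.

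Table 5 lists 23 active tests for weeks 1 to 5. Twenty have two day slots a week. Three have one: mSDMT (Day 1), Adlerauge (Day 3) and Nebel (Day 3). Week 6 holds only questionnaires and the interview. Section 3.5.1 also states: "Users will not be able to perform challenges or play games outside the schedule".

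Table 3 lists Adlerauge and Nebel as the only vision challenges. Section 11.1 names four domains in the alternative hypothesis: "a) vision b) cognition c) dexterity d) movement".

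**The concern.** A repetition count that the reliability criteria are written around is not what the schedule delivers for three tests, and two of those are the entire vision domain. Even a participant who completes everything contributes 5 vision measurements, not 10. The two free days each week take only postponed exercises, so they add none.

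Three things are at stake. First, anyone applying the section 6.1 criteria literally finds that they describe a condition the vision tests never reach, and would have to decide after the fact how to read them. Second, the vision and mSDMT estimates are less precise than the text implies. Third, the median of individual CVs depends somewhat on the number of repeats, so the same 20% cut-off is slightly more lenient with 5 repeats than with 10.

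**Working it through.** **Inputs.** Test durations, day slots and footers come from Table 5; the 5 active weeks and n = 30 per group from section 6.1; the thresholds and the median-CV definition from section 11.4.2; the 80% adherence minimum from Step 2 of that section.

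**1. Is the table read correctly?** Adding the durations in each day column and comparing with the footers:

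| Day | Seconds | Minutes (sum) | Minutes (footer) | Challenges (count) | Challenges (footer) |
|---|---|---|---|---|---|
| 1 | 610 | 10.2 | 10.2 | 7 | 7 |
| 2 | 640 | 10.7 | 10.7 | 7 | 7 |
| 3 | 620 | 10.3 | 10.3 | 11 | 11 |
| 4 | 580 | 9.7 | 9.7 | 7 | 7 |
| 5 | 660 | 11.0 | 11.0 | 11 | 11 |

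Both footers reproduce exactly with single slots for the three tests. A cell lost in conversion would break the sums.

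**2. Repetitions.** Repetitions = slots per week × 5.
- 20 tests: 2 × 5 = 10, as stated.
- mSDMT, Adlerauge, Nebel: 1 × 5 = 5.
- Weekly slots: 20 × 2 + 3 × 1 = 43. Twice weekly for all would be 23 × 2 = 46.
- Per participant: 43 × 5 = 215 against 46 × 5 = 230, a shortfall of 15 (6.5%), all in these three tests.

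**3. Effect on the CV criterion.** Assume normal within-participant data, a CV common to all participants, and each participant's mean treated as known. The median sample CV is then the true CV times c(k) = √(median of χ² with k − 1 df ÷ (k − 1)), and the 20% cut-off corresponds to a true CV of 20% ÷ c(k).

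| Completed repeats k | c(k) | True CV at the 20% cut-off |
|---|---|---|
| 10 (all of 10) | 0.963 | 20.8% |
| 5 (all of 5) | 0.916 | 21.8% |
| 8 (80% of 10) | 0.952 | 21.0% |
| 4 (80% of 5) | 0.888 | 22.5% |

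The comparisons at equal adherence are 21.8% against 20.8%, and 22.5% against 21.0%. The relative standard error of one participant's SD, and so roughly of the individual CV, is 1/√(2(k − 1)): 24% with 10 repeats and 35% with 5.

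**4. Effect on the ICC criterion.** One-way ICC, exact F distribution, n = 30. For an observed ICC of 0.6 the 95% interval is 0.47 to 0.74 with 10 repeats and 0.44 to 0.75 with 5. The probability of observing at least 0.6 is:

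| True ICC | 10 repeats | 5 repeats |
|---|---|---|
| 0.50 | 6.7% | 9.9% |
| 0.60 | 47.0% | 47.6% |
| 0.65 | 73.7% | 71.8% |
| 0.70 | 91.2% | 89.3% |

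Five repeats discriminate slightly less well in both directions; the ICC gate is not materially easier.

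**The case against.** The strongest reply is that the analysis is not blocked. Section 11.4.2, to which 6.1 defers, sets its thresholds without a repeat count, and adherence is measured against each test's own scheduled repetitions. Both statistics can be calculated from 5 repeats. This stands. A reader might infer that the vision tests and mSDMT cannot meet the reliability criteria at all. The documents do not support that: the wording in 6.1 is wrong for three tests, but the operative thresholds still work.

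A reader might also infer that the Step 3 ranking compares unequal tests. Step 3 ranks within each domain, and the two vision tests both have 5 repeats, so they are ranked like for like. Only mSDMT sits in a domain with 10-repeat tests. Step 1 names movement, vision and dexterity but not cognition, so whether mSDMT faces the section 11.4.2 reliability gate is itself unclear; for mSDMT the 10-repeat wording comes from 6.1, which speaks of each biomarker. Cognition also keeps ten PEAK games at 10 repeats.

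Setting 4 repeats against a full 10 would enlarge the CV effect unfairly. At the same 80% adherence the other tests have 8.

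Finally, it is tempting to replace the median CV with a pooled within-participant CV. That is a different quantity, equal to the typical individual CV only if all participants share one. In a simulation with n = 30, 10 repeats, a typical CV of 15% and an assumed log-SD of 0.5 between participants, the median passed 20% in about 99.7% of runs and the root mean square in about 65%. The change could move the gate far more than the one-point shift it would correct.

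None of this removes the contradiction. Section 3.5.1 words 10 repeats as an aim, but the synopsis and 6.1 state it as fact.

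**Conclusion.** The contradiction holds and should be fixed. The count of 10 reproduces for 20 of the 23 active tests and fails for mSDMT, Adlerauge and Nebel, which have 5. Only vision is affected as a whole domain, and the vision part of the hypothesis rests on half the stated repetitions.

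The statistical consequence is modest: roughly one percentage point on the true CV that the 20% cut-off corresponds to (1.5 points at 80% adherence), noticeably less precise individual CVs, and a slightly wider ICC interval. The CV figures assume normality and a common CV; the ICC figures assume a one-way model with 30 participants. This is a feasibility study with no formal sample size calculation, and its selections go to a separate validation study, so the point is one to correct and not one that invalidates the design. The documents do not show which frequency was intended.

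**What to change.** Reconcile the synopsis, section 3.5.1, section 6.1 and Table 5 before launch, in one of two ways.

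1. Keep Table 5. State in the synopsis, 3.5.1 and the 6.1 criteria that mSDMT, Adlerauge and Nebel have 5 scheduled repetitions and all other tests 10. The cost is a wording change.
2. Keep the text. Give the three tests a second weekly slot in Table 5. This adds 90 + 30 + 30 = 150 s (2.5 min) a week. Even if all of it fell on the longest day, that day would reach 11.0 + 2.5 = 13.5 min, within the stated maximum of 15 to 20 min. The cost is a change to the app schedule and the Table 5 footers.

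The median CV in section 11.4.2 can stay as specified under either option. The second option is useful only before testing, because missing repetitions cannot be recovered afterwards.

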### **6.2 Methods of minimising bias**

Not applicable.

#### **6.2.1 Randomisation**

Not applicable.

#### **6.2.2 Blinding procedures**

Not applicable.

### **6.2.3 Other methods of minimising bias**

Not applicable.

### **6.3 Unblinding Procedures (Code break)**

Not applicable.

## 7. STUDY POPULATION

### 7.1 Eligibility criteria

Participants fulfilling all of the following inclusion criteria are eligible for the study:

#### A. Participants with MS

- Age 18-70
- Diagnosed with MS according to the revised McDonald criteria 2017, all clinical forms inclusive (CIS, RRMS, SPMS, PPMS)
- EDSS  $\leq$  6.5
- In possession of a DREAMS App compatible smartphone (iOS/Android, see section 3.2.4, Table 2)
- Corrected close visual acuity of  $\geq$ 0.5
- Hand motor skills sufficient for using a smartphone
- Ability to follow the study procedures
- Informed Consent as documented by signature

#### B. Healthy controls (sex and age matched to patients)

- Age 18-70
- In possession of a DREAMS App compatible smartphone (iOS/Android, see section 3.2.4, Table 2)
- Corrected close visual acuity of  $\geq$ 0.5
- Hand motor skills sufficient for using a smartphone
- Being able to walk without aid
- Ability to follow the study procedures
- Informed Consent as documented by signature

The presence of any one of the following exclusion criteria will lead to exclusion of the participant:

#### A. Participants with MS

- Other clinically significant concomitant disease states (e.g., renal failure, severe hepatic dysfunction, severe/unstable cardiovascular disease, progressive cancer, etc.)
- Known or suspected non-compliance, drug or alcohol abuse
- Women who are pregnant or breast feeding
- Being a frequent PEAK\* user (having used PEAK  $\geq$  once daily over a period of  $\geq$ 3 weeks) and not willing not to use PEAK during the study period

\* PEAK: freely available App for cognitive training

#### B. Healthy controls (sex and age matched to patients)

- Being diagnosed with MS or other disease affecting neurological and cognitive functions
- Other clinically significant concomitant disease states (e.g., renal failure, severe hepatic dysfunction, severe/unstable cardiovascular disease, progressive cancer, etc.)

- Known or suspected non-compliance, drug or alcohol abuse
- Women who are pregnant or breast feeding
- Being a frequent PEAK\* user (having used PEAK  $\geq$  once daily over a period of  $\geq 3$  weeks) and not willing not to use PEAK during the study period

\* PEAK: freely available App for cognitive training

## 7.2 Recruitment and screening

Patients will be recruited at the MS Center Basel (Department of Neurology, University Hospital Basel, Basel, Switzerland).

Patients will be asked during their (regular) clinical visits to participate, will be provided with information and will be asked to think about a possible participation. Once willing to participate, they will be invited for the screening visit. The clinical information will be documented from the latest clinical visit (patient history, medication, EDSS, MSFC (Multiple Sclerosis Functional Composite (T25FW, 9-HPT)) and SDMT (Symbol Digit Modalities Test)).

If patients are included and some of the tests have not already been performed, these will be performed at Screening or Baseline. In addition to the standard tests we will also perform a neuropsychological assessment (see chapter 9 study assessment), near vision acuity and contrast vision assessment.

Healthy controls will be recruited via advertisements and amongst relatives of patients attending the clinic and will be invited for screening if willing to participate. Healthy controls have to be included sex- and age- matched to patients and therefore will be recruited accordingly.

## 7.3 Assignment to study groups

Not applicable.

## 7.4 Criteria for withdrawal / discontinuation of participants

Patients and healthy controls will be withdrawn from the study if the following occurs during the study period:

- Other clinically significant concomitant disease states (e.g., renal failure, severe hepatic dysfunction, severe/unstable cardiovascular disease, progressive cancer, etc.)
- Non-compliance
- Inability to follow the procedures of the study, e.g. due to language problems, psychological disorders, dementia, etc. of the participant
- Pregnancy: If a participant will realise pregnancy during the study period, she should contact the study nurse. The participant will be allowed to continue the study if she wants to but of course can also withdraw consent immediately.
- Loss of their DREAMS App compatible smartphone (iOS/Android, see section 3.2.4, Table 2)
- Close visual acuity loss of  $< 0.5$
- Loss of hand motor skills not sufficient for using a smartphone
- Using PEAK\* during the study period

\* PEAK: freely available App for cognitive training

Withdrawn participants (drop-out) will be replaced by an additional participant.  
Data of withdrawn participants collected until withdrawal will not be deleted and will be used in a coded form for research purposes.

